### 2.5. Intervention

#### 2.5.1. Medication

During the baseline screening phase, all participants will not receive any psychiatric medication as there is no immediate risk and treatment indication. Participants were tracked for the medication during the study. They are not restricted in their medication and have access to regular help in this process. If participants take medication during the study, a record will be kept.

#### 2.5.2. Wait list control group

Participants in this control group will be on a waiting list for 4 months. Afterward, they will receive the self-help micro-video psychological intervention after the study. A waiting list control group is ethically acceptable given that there is no immediate risk or indication for medical treatment (31). At the same time, all members of the wait-in-list will also be screened for regular monitoring and preparedness for emergency intervention protocols and referrals to clinical services as necessary. During this time, they will have unrestricted access to professional help if necessary. The only difference with the intervention group is whether self-help methods are actively taught.

#### 2.5.3. Micro-video psychological intervention group

##### 2.5.3.1. Technical overview and customization

After random assignment, the participants in the micro-video psychological intervention group will enter the *MVPTC* and take eight group sessions of micro-video intervention every 3 days. *MVPTC* is an online, self-service smartphone applet with assessment and intervention functions and content such as mindfulness audio recordings and articles on psychoeducation. Many additional functions are under development. The virtual psychotherapist, Xiao Wei, as named by the SMHC, is the training’s virtual guide. The word “Wei” in the name “Xiao Wei” in Chinese denotes tenderness, support, and simplicity, representing that Xiao Wei will guide the participants when they are depressed and anxious in a simplified and supportive form of psychotherapy.

*Micro-Video Psychological Training Camp* is a micro-video self-service psychological intervention platform on WeChat applets. The goal of this platform is to address the current issue of limited psychotherapy resources, rather than replace psychotherapy. After designing the knowledge structure and picking content for the *MVPTC*, psychiatric and psychological professionals at SMHC delve deeper into the platform and its development by reading up on related literature involving the psychological treatment of depression and anxiety. During this period, they frequently scheduled meetings to discuss the outline, compose and modify its script, make animations, and develop its program. After completing preliminary development, user experience tests and interviews with participants were carried out. Later, the intervention content and applet were further improved based on the feedback. Finally, the final launch was completed within a year and is continually improved and upgraded.

On WeChat, the most frequently used app in China, the *MVPTC* applet platform is easily accessible to users. Participants can use the platform conveniently in the privacy of their own homes, with more flexibility, and in a relatively anonymous way. Mandatory hospital or treatment room visitations can be reduced after using this platform, and it brings a lot of convenience for participants even in this pandemic era, no matter where they are. This can save transportation time and streamline the treatment process. In addition, the platform’s online application can reduce the time spent with clinicians while minimizing costs, which can make intervention treatment accessible to more populations.

By using the management system of the applet, all participants can be monitored and tracked by the researchers. While the platform does not have a crisis management function, when participants in both groups face the risk of self-injury, suicide, or exacerbating their symptoms of depression and anxiety, researchers still have the option of halting the study after discussed with the research team. Furthermore, participants in this situation can be recommended by researchers to receive emergency medical treatment. If necessary, the participant’s guardian or family member can be contacted to talk about the possible need for higher-level treatment, such as medication or hospitalization. All of this will be informed consent at the beginning of the study.

##### 2.5.3.2. Integrative support approach

After logging into the WeChat applet and completing the registration, participants will receive a brief welcome message that invites them to participate in the intervention treatment. Here, they will be provided with the necessary information that overviews the intervention form, intervention module, operation, and functions of the intervention treatment. After finishing the opening message, participants can complete the intervention more smoothly.

*Micro-Video Psychological Training Camp* delivering therapy is primarily grounded on the core techniques and principles of CBT (32, 33), integrating psychoeducation, mindfulness (34–36), dialectical behavior therapy (37), as well as interpersonal psychotherapy (38), all of which have proven efficacy in empirical studies on emotional issues including depression, anxiety, and mental resilience. By properly regulating various aspects in terms of emotional, cognitive, behavioral, and interpersonal functions, this therapy can effectively alleviate the effects of depression and anxiety while building up mental resilience. Guided by the virtual therapist Xiao Wei, the therapy content is presented in the form of vivid animation by combining visuals and audio. The duration of these micro-videos in each section ranges from 3 to 5 min and can be repeatedly watched. There is one module every 3 days, for a total of eight treatment modules. Moreover, relevant tasks or homework will be assigned at the final stage of each session. Here, participants can complete them on a self-help basis. A brief review of the session content will also be provided so that participants can apply their knowledge in a flexible and accurate manner. There will also be some optional supplemental resources available on the platform, such as mindfulness audio recordings, which can be downloaded at will.

The eight treatment modules are listed as follows: one of the modules is about psychoeducation involving stress, emotions, and our reactions to them; two of the modules are on emotional regulation and involve the identification and management of our emotions, the stabilization of our emotions, and how to be the master of our emotions; one of the modules is on behavior activation; one deals with problem-solving; one concerns communication skills and interpersonal support; one is related to cognitive reconstruction; and one of the modules is concerned with mindfulness. The screenshot startpage, sessions, and homework are shown in Figure 2.

**FIGURE 2 F2:**
[figure not shown]
Screenshot startpage, sessions, and homework.

A total of eight specific treatment modules are recommended for each participant in a specific order. They can keep returning to the system and writing down what they have practiced every day, which can be viewed again after recording. This method can enhance user engagement in the homework feedback and interactions, affording participants the chance to apply the techniques they have learned in everyday life, thereby bolstering and consolidating the effects of the treatment protocol.

To encourage participants to continue to study and practice online, the camp gives participants automatic reminders and notification messages in a compassionate and supportive way. Some examples of the sample content are as follows: “(nickname), hello! Today you can start the 6th training session on the “*Micro-Video Psychological Training Camp*” applet to learn about communication skills to help improve your interpersonal support. Please log in to the applet in time to complete this training. I hope to see you make progress!” When participants complete a module, the reminders “You did an awesome job” and “Keep it up” will be displayed on the screen.

### 2.7. Sample size

The results of the pre-experiment were used as a reference for the estimation of the sample size. The preliminary results of the intervention group before and after the intervention in the pre-experiment are shown in Table 1.

From previous studies (39), we know that there was no significant statistical difference between the result of the waiting list control group’s score before and after. Thus, we used the score before the intervention as the outcome score of the waiting list control group and the score after the intervention as the outcome score of the intervention group to calculate the sample size that was based on the two-sample mean to improve the efficiency of the experimental design (40) in the calculation formula when computing the sample size.

(1)
$$\eta_{A}=\kappa \eta_{B}\text{⁢and⁢}\eta_{B}=(1+\frac{1}{k}\,){\left(\sigma \frac{z_{1-\alpha }+z_{1-\beta }}{\mu_{A}-\mu_{B}-\delta }\right)}^{2}$$

κ represents the ratio of two groups of sample size. In this study, κ = *1*. σ stands for standard deviation. In this study, the standard deviation before intervention was considered the population standard deviation. *Z1*-α represents the value of the standard normal distribution function corresponding to the level of class I error (test level). *Z1*-β represents the value of the standard normal distribution function corresponding to the level of class II error (test level); Delta represents the boundary between the two sets of values.

The test level α = 0.05 and the degree of certainty β = 0.20 were set. The combined standard deviation of SDS and SAS as well as the boundary values of different outcome indices (the difference between indices considered to be meaningful professionally) were used to calculate the sample size, as the results are shown in Table 2. In light of feasibility, funding, and other practical factors, the study selected 100 cases in each group, or 200 cases in total, as the sample size.

**TABLE 2 T2:** Minimum sample size of each group required to find differences between groups at different threshold levels.

Outcome indicators	Outcome score of intervention group	Outcome score of control group	Combined standard deviation σ	Boundary value δ	Sample size	Loss rate 30%
SDS	50	61	8	5	22	33
				6	32	43
				7	50	61
				8	88	98
				9	198	209
SAS	42	51	7	4	25	36
				5	38	49
				6	68	79
				7	152	163

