## 5. Discussion

This online trial will examine whether a self-help psychological intervention platform that helps alleviate depression and/or anxiety symptoms and enhance resilience will be effective in terms of clinical outcomes and applicability.

This study has several inherent limitations. First, there may be dropouts in either of the two groups. We will conduct a dropout analysis and a survey to examine the reasons why the dropouts withdrew from the study. Second, since we will only use self-report questionnaires instead of examiner-rating scales or formal diagnostic instruments, there may be a bias resulting from the participants knowing their group. In addition, the elderly and participants with severe symptoms may have some inconvenience when using their mobile phones for online measurement. We opted for self-rating because, theoretically, the measurement and intervention should be easily accessible and highly applicable. Third, we anticipate that younger people, more psychologically engaged individuals, or more motivated people will be attracted by this open recruitment strategy. Accordingly, we should be cautious when generalizing results about a certain type of population. Finally, using a waiting list trial design poses substantial limitations on the validity and universality of the results. Mild to moderate depression and anxiety symptoms have a tendency to heal on their own, and there is also a probability that the control group will also take various self-help measures, which would underestimate the intervention effect of our study.

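### Table 2's 30% loss column adds a flat 10 or 11 people per row instead of dividing by 0.7, so 100 per group does not cover SDS boundary 8 as it appears to

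*Protocol article*

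**What the plan says.** Section 2.7 of the protocol article sizes the trial with a two-sample formula for means that subtracts a boundary δ from the expected group difference, with equal groups. On error rates it says: "The test level α = 0.05 and the degree of certainty β = 0.20 were set".

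Table 2 applies the formula to five boundaries for the SDS and four for the SAS. Its columns are intervention mean, control mean, SD, boundary, size per group, and size per group with 30% loss. The first SDS row reads "SDS 50 61 8 5 22 33" and the first SAS row "SAS 42 51 7 4 25 36"; later rows change only the boundary and the two sizes.

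The text then cites practical grounds, among them money and feasibility, and concludes that "the study selected 100 cases in each group, or 200 cases in total, as the sample size". It names no boundary as the design target and does not explain how the loss column was obtained. Section 5 accepts that "there may be dropouts in either of the two groups" but gives no rate, so this column is the only place where the article quantifies withdrawal.

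**The concern.** A percentage allowance must grow with the size it is applied to. Here the no-loss sizes run from 22 to 198, yet the increment hardly moves. If the column is wrong, larger rows carry progressively less protection than the heading states.

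The consequence is sharpest near the chosen size. The printed 98 at SDS boundary 8 lies just below 100, so a reader comparing the two will take that boundary as covered with 30% withdrawal. The SDS is one of the two primary measures, and the article presents the boundary as a professionally meaningful difference. The table would therefore overstate what the trial can show on a primary outcome.

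**Working it through.** **Inputs (Section 2.7 and Table 2).** α = 0.05 and β = 0.20 (80% power), with the one-sided quantile as in formula (1); allocation 1:1. SDS: means 50 and 61, difference 11, SD 8. SAS: means 42 and 51, difference 9, SD 7. Loss 30%.

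**Step 1: reproduce the no-loss column.** With equal groups, formula (1) is n = 2 × [σ × (1.645 + 0.842) / (difference − δ)]², taking the size of the difference.

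- SDS, δ = 8: 2 × (8 × 2.486 / 3)² = 87.9, rounded up to 88, as printed.
- SAS, δ = 6: 2 × (7 × 2.486 / 3)² = 67.3, rounded up to 68, as printed.

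All nine no-loss sizes reproduce in this way. A two-sided quantile does not reproduce them (it gives 112 at SDS 8). The table was therefore read intact, and any error is confined to the last column.

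**Step 2: test the loss column.** The implied loss is 1 − n / (printed size with loss). The correct size for 30% loss is n / 0.7, rounded up. The looser n × 1.3 is shown in case it was the rule used.

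| Row | n | Printed with loss | Added | Implied loss | n / 0.7 | n × 1.3 |
|---|---|---|---|---|---|---|
| SDS 5 | 22 | 33 | 11 | 33% | 32 | 29 |
| SDS 6 | 32 | 43 | 11 | 26% | 46 | 42 |
| SDS 7 | 50 | 61 | 11 | 18% | 72 | 65 |
| SDS 8 | 88 | 98 | 10 | 10% | 126 | 115 |
| SDS 9 | 198 | 209 | 11 | 5% | 283 | 258 |
| SAS 4 | 25 | 36 | 11 | 31% | 36 | 33 |
| SAS 5 | 38 | 49 | 11 | 22% | 55 | 50 |
| SAS 6 | 68 | 79 | 11 | 14% | 98 | 89 |
| SAS 7 | 152 | 163 | 11 | 7% | 218 | 198 |

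Neither rule generates the column. Division by 0.7 matches exactly at SAS 4 and is within one at SDS 5, where the printed figure is one too many. Multiplication by 1.3 comes within one only at SDS 6 and SAS 5. Seven of the nine entries fall short of a 30% allowance. At SDS 8 both rules give more than 100.

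**Step 3: what 100 per group supports.** After 30% loss, 100 × 0.7 = 70 remain.

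- Power at SDS boundary 8 with 70 per group: Φ[3 / (8 × √(2/70)) − 1.645] = Φ(0.574) = 71.7%. With all 100 it is 84.3%.
- Largest SDS boundary with 80% power at 70 per group: 11 − 8 × 2.486 × √(2/70) = 7.64.
- Largest loss that keeps the required 88 out of 100: 1 − 88/100 = 12%.
- SAS boundary 6 with 70 per group: power 81.3%, so still covered.

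**The case against.** The arithmetic is hard to dispute; the case on the other side is about consequence.

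- **No target boundary.** The article chooses 100 on practical grounds and never claims that 100 covers SDS boundary 8. This stands: coverage of that boundary is what the table implies, not what the text asserts. But when the size is fixed by practicality, the table's job is to say what that size can detect, and at this row it says so wrongly.
- **One row changes sides.** With the column corrected, 100 per group still covers SDS 5 to 7 (32, 46, 72) and SAS 4 to 6 (36, 55, 98). SDS 9 and SAS 7 were already beyond 100 as printed (209 and 163). This stands too: only SDS 8 moves from covered to not covered, and SAS coverage at 100 is unaffected.
- **The planned analysis tests no boundary.** Section 4 plans t-tests and a repeated-measures group × time comparison, with no boundary stated. A two-sided test of zero difference on the table's own differences and SDs needs only 9 (SDS) or 10 (SAS) per group. Even if one assumes half the SDS difference (5.5) and the larger post-intervention SD from Table 1 (10.11), 70 per group gives about 90% power. This also stands, and it limits how the 72% may be read: it is power against boundary 8, not the trial's power to detect any difference.

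None of this makes the column correct.

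**Conclusion.** The concern holds. The column headed as a 30% loss is not one. It adds a near-constant 10 or 11 people, and the loss actually allowed for ranges from 33% down to 5%. Seven of nine entries are too small, at worst 209 printed against 283 needed.

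The practical effect falls on SDS boundary 8, which needs 126 per group rather than 98 and is not covered by 100 with 30% loss: power against it is 72%, and the largest SDS boundary supported is about 7.6. These figures take as given the article's one-sided formula, rounded means and SDs, no-loss sizes and 30% loss rate. The conclusion concerns the stated coverage of boundaries. It does not show the trial to be underpowered for a test of no difference under the table's assumptions.

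**What to change.** Recompute the loss column as n / 0.7, rounded up: 32, 46, 72, 126, 283 for the SDS and 36, 55, 98, 218 for the SAS. Then add one sentence to Section 2.7, in one of two forms:

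- 100 per group with 30% loss leaves 70, which on the table's inputs supports SDS boundary 7 (up to about 7.6) and SAS boundary 6, but not SDS boundary 8; or
- 100 per group supports SDS boundary 8 provided that loss does not exceed 12%.

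The cost is one corrected column, one sentence, and a slightly less favourable statement of what the trial can detect. Neither the enrolment of 200 nor the conduct of the trial has to change.

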### 2.8. Discontinuation

If the below conditions are met, participants will be able to choose to withdraw or will be required to quit the study:

a.Somatic disease progression.b.Serious adverse events.c.Uncontrollable concurrent disease.d.Whenever the participant wishes to withdraw.e.Poor compliance.f.Instances in which withdrawal from the study can bring more benefits to the participants, including adverse health factors or an increased risk of suicide.

Participants should be clearly informed of their right to withdraw from the study at any time, regardless of their stage of evaluation, treatment, or follow-up. The principal investigator is responsible for the decision to withdraw a participant from the study after consulting other members of the team.

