## 3. Outcome measurements and instruments

The study assessment will be completed online by the subjects on a self-help basis. Self-rating scales were used in this study. The analysis of these scales will be conducted by a statistician without knowing how the subjects are allocated.

The efficacy indicators include (1) the primary outcome: the change in the SDS score and the SAS score between groups at different times. In particular, if the reduction rate is ≥50%, an obvious effect will be shown; if the rate is <50 and ≥25%, the effect is only average; and if the rate is <25%, no clinical effect will exist. (2) The secondary efficacy outcome is based on The Connor-Davidson Resilience Scale (CD-RISC) score, which can be increased as symptoms of anxiety and depression improve during the treatment process. In addition, measurements including the Insomnia Severity Index (ISI) and the Perceived Social Support Scale (PSSS) will be provided.

The applicability indicators include the intervention completion rate, the dropping rate, and the Self-Assessment Scale of the Overall Efficacy and Satisfaction of Participants (SASE) score.

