## 4. Statistical analysis

The analyses will be conducted based on the principle of intention-to-treat, meaning that all participants who have been randomized will be included in the analyses. In statistical tests, the SPSS version 23.0 software will be selected and used. The relevant data will be considered statistically significant if P < 0.05. The categorical variables are statistically described by the number of cases (percentage), and the chi-square analysis is used for intergroup comparison. Continuous variables are statistically described using mean ± standard deviation (M ± SD), and the independent sample *t*-test is used to make comparisons between the two groups. Also, repeated measures, such as ANOVA, are used to compare the degree of symptom improvement between the intervention group and the control group, and the interaction of group × time is analyzed. Missing data will be imputed using the estimation maximization (EM) method in SPSS version 23.0.

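### Participants may be required to quit the study for poor compliance, which would fall mainly on the intervention arm; their later outcomes would then be imputed, not observed, which could bias the intention-to-treat comparison towards the intervention

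*Protocol article*

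**What the plan says.** **Leaving the study.** Section 2.8 gives six conditions (a to f) under which "participants will be able to choose to withdraw or will be required to quit the study". Item e is "Poor compliance", with no definition. Item d separately covers a participant's own wish to withdraw. On authority, the section says: "The principal investigator is responsible for the decision to withdraw a participant from the study after consulting other members of the team".

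**What there is to comply with.** Section 2.5.3.2, on the intervention: "There is one module every 3 days, for a total of eight treatment modules". Each session ends with homework. Section 2.5.2, on the control arm: "Participants in this control group will be on a waiting list for 4 months". Control participants get the modules only after the study. The Abstract plans online self-assessments at baseline, post-intervention, 1 month and 3 months, and does not limit them to one arm.

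**Analysis.** Section 4 commits to intention-to-treat, so that "all participants who have been randomized will be included in the analyses". It adds: "Missing data will be imputed using the estimation maximization (EM) method in SPSS version 23.0".

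**Outcomes that depend on withdrawal.** Section 3: "The applicability indicators include the intervention completion rate, the dropping rate", together with a satisfaction score. Section 5 plans a dropout analysis and a survey of reasons.

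**The concern.** Item e concerns leaving the study, not only stopping the modules. Since item d already covers participant choice, item e adds little unless withdrawal for poor compliance can be imposed.

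The activity most likely to be judged for compliance, eight modules with homework over 24 days, exists in one arm only. Not using the intervention is also plausibly related to outcome. The plan can therefore itself create missing outcomes that differ by arm and relate to the result. EM relies on data being missing at random given what is observed. The first assessment after baseline comes at the end of the 24 days, so anyone removed during the modules would have baseline scores only.

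Two results are at stake. The primary SDS and SAS comparison could be shifted towards the intervention. The dropping rate, meant to show whether people stay with the platform, would partly record decisions by the study team.

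**Working it through.** **Inputs from the documents.** Table 2 takes an SDS outcome score of 50 in the intervention group and 61 in the control group, so D = 61 − 50 = 11 points. Section 2.7 plans 100 per arm.

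**Check that 11 is the plan's working difference.** Put into the article's formula with σ = 8, boundary 5, α = 0.05 and β = 0.20: n = 2 × (8 × (1.645 + 0.842) / (11 − 5))² ≈ 22 per group, which is Table 2's entry. All nine entries in the Sample size column reproduce in the same way. The concern changes none of them.

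**Assumptions not in the documents.**
- A share q of the intervention arm is required to quit for poor compliance before any post-baseline assessment. Values of 0–30% are shown. The only loss figure in the article is a 30% planning rate for all causes.
- Removed participants get a fraction f of the compliers' benefit. The main illustration uses f = 0.
- There are no losses in the control arm, and baseline scores do not separate compliers from non-compliers.

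**Formulas.**
- True intention-to-treat effect = D × [(1 − q) + q × f].
- The imputation in effect credits removed participants with a fraction g of the compliers' benefit, so the estimate = D × [(1 − q) + q × g].
- Bias = q × D × (g − f).

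Section 4 does not say how EM is set up, so two cases bracket g:
- Filled from intervention-arm compliers: g = 1.
- Filled from the pooled mean of all observed participants: g = (1 − q) / (2 − q).

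Pooled case at q = 0.20: observed mean = (80 × 50 + 100 × 61) / 180 = 56.11. Intervention mean after filling = 0.8 × 50 + 0.2 × 56.11 = 51.22. Estimate = 61 − 51.22 = 9.78, against a true 8.8.

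Pooled case at q = 0.30: observed mean = (70 × 50 + 100 × 61) / 170 = 56.47. Intervention mean after filling = 0.7 × 50 + 0.3 × 56.47 = 51.94. Estimate = 61 − 51.94 = 9.06, against a true 7.7.

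**Results with D = 11 and f = 0.**

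| q | True effect | Pooled filling: estimate | Overstatement | Filling from compliers: estimate | Overstatement |
|---|---|---|---|---|---|
| 0 | 11 | 11 | 0 | 11 | 0 |
| 10% | 9.9 | 10.4 | 0.5 (5%) | 11 | 1.1 (11%) |
| 20% | 8.8 | 9.8 | 1.0 (11%) | 11 | 2.2 (25%) |
| 30% | 7.7 | 9.1 | 1.4 (18%) | 11 | 3.3 (43%) |

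With f = 0 the percentages do not depend on D.

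**Sensitivity to f.** With f = 0.5, filling from compliers overstates by half as much in points: 1.1 at q = 20% and 1.65 at q = 30%. Under pooled filling, g is 0.44 at q = 20% and 0.41 at q = 30%, so f = 0.5 slightly reverses the bias: 0.20 × 11 × (0.444 − 0.5) = −0.1 points. The bias favours the intervention only when removed participants do worse than the values credited to them.

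**The case against.** **Only the intervention arm can be non-compliant.** A reader might infer this, but the article does not say it. Compliance is undefined and item e is not limited to one arm. Control participants have repeated questionnaires and regular monitoring, and could be poorly compliant with those. What stands is that module and homework compliance can fail only in the intervention arm, so removals would be expected mainly there.

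**Non-compliers drop out of the intention-to-treat analysis.** A reader might infer this too. Section 4 keeps every randomized participant through imputation. What is lost is the observed outcome, not the place in the analysis.

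**Removal is not automatic.** Section 2.8 mixes voluntary and required exit, does not say which conditions compel it, and leaves the decision to the principal investigator after consulting the team. This stands: the article sets a discretionary power, not a fixed rule. Discretion in an open trial is little reassurance, because only the statistician is described as unaware of allocation.

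**Follow-up after withdrawal may be set out in the full protocol.** This is fair, and silence in a condensed article is no finding. The point rests on what is written: a ground for quitting the study that sits badly with an analysis meant to use everyone's outcomes.

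**The larger percentages are a worst case.** This also stands. EM may pool the arms, may use a participant's own scores, and some people may stop modules because they have improved; Section 5 notes natural recovery.

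**The applicability effect is limited.** Someone who skips modules would generally count as a non-completer whether removed or not, so the completion rate changes little. The dropping rate is affected more directly. The planned survey of reasons helps, but the article does not say that it separates imposed from chosen withdrawal.

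**Conclusion.** The concern holds in a limited form. The article allows participants to be required to leave the study for undefined poor compliance, in a trial where the main thing to comply with exists in one arm. On the natural reading, this creates outcome-related missing data that differ by arm, and EM under missing at random does not repair it. Section 2.8 and Section 4 need to be reconciled.

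The size cannot be known from the documents. It is zero if nobody is removed on this ground or if outcomes are still collected. If 20–30% of the intervention arm were removed with no benefit, the 11-point SDS effect would be overstated by 1.0–1.4 points under pooled filling and by up to 2.2–3.3 points under filling from compliers. Both the share removed and their lack of benefit are assumptions. The documents therefore support saying that the comparison could be biased towards the intervention, not that it will be. Section 5 expects the wait-list design to understate the effect and does not mention this possible bias in the other direction.

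This should be fixed, since outcomes never collected cannot be recovered at analysis, but it does not undermine the design as a whole.

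**What to change.** Reconcile Section 2.8 with Section 4 by separating stopping the modules from leaving the study:

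- State that poor compliance with modules or homework does not end study participation. Anyone who stops or skips modules stays in follow-up for the online SDS and SAS at post-intervention, 1 month and 3 months, unless they withdraw consent.
- Record module compliance as an applicability outcome.
- In the dropout analysis already planned in Section 5, report withdrawal started by the participant separately from withdrawal imposed by the investigator, by arm.

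The safety-related grounds in Section 2.8 stay as they are.

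The cost is a change of protocol wording and a few reminder messages to people who have stopped the modules. The questionnaires are already online.
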